# Research Objectives

## General Objectives

### To rigorously evaluate the efficacy of the microclinic social network intervention on the ‘kinetics’ of engagement in the HIV cascade of care, as well as other clinical outcomes, on Mfangano, Ringiti and Remba Islands.

### To evaluate essential implementation science parameters of the microclinic social network intervention.

## Specific Objectives

### To understand the efficacy of the microclinic social network intervention on:

### engagement in HIV care over time among patients who are at particularly high risk for disengaging from care.

### re-engagement in care following a missed clinic appointment.

### overall retention in care after one year of follow-up

### To understand implementation parameters of the microclinic social network intervention, in particular:

### Cost-effectiveness measures of the intervention per patient retained

### Fidelity of implementation of a complex social network intervention in remote island clinic settings

### Adoption of intervention among diverse populations on three different islands

# Design and Methodology

## Study site

The study will be conducted on Mfangano, Ringiti and Remba Islands, Homa Bay County, Kenya. This study will be coordinated out of the Ekialo Kiona Center on Kitawi Beach, Mfangano Island. Index participant enrollment and data collection will occur at any of the FACES-supported Ministry of Health clinics on the three islands (Table 1). Patients who receive HIV care and treatment at any of these clinics and who miss a clinic visit by >3 days will be eligible for participation in the study. Patients residing in the Mfangano East sub-location will be excluded from participation in this study as we previously conductd a pilot study offering all patients in that geographc area the opportunity to participate in the microclinic intervention. Data will be analyzed by investigators at KEMRI, UCSF, MCI, and OHR.

| **Health Center** | **Current adult patients** | **Current adult patients on ART** |
| --- | --- | --- |
| **Mfangano Island Total** | **1,380** | **856** |
| Sena HC | 549 | 427 |
| Ugina HC | 153 | 66 |
| Wakula HC | 397 | 185 |
| Yokia HC | 192 | 131 |
| Nyakweri HC | 49 | 33 |
| Soklo HC | 40 | 14 |
| **Ringiti Island Total** | **111** | **78** |
| Ringiti HC | 111 | 78 |
| **Remba Island Total** | **234** | **147** |
| Remba HC | 234 | 147 |
|  |  |  |
| **Total patient population** | **1,725** | **1,081** |
| **Table 1.** Health center adult patient populations on Mfangano, Remba and Ringiti Islands | | |

## Study population

### Subject Inclusion Criteria

- Must be currently receiving combination antiretroviral therapy (cART) or co-trimoxozole prophylaxis from one of the eligible study clinics:
  - Is currently in care at study baseline, defined as having ≥1 medical care visit to receive medications (cART or prophylaxis) during the six months preceeding initiation of study enrollment, OR
  - Initiates pre-ART or ART care for the first time at a study clinic during the six month study recruitment period, OR
  - Transfers from a clinic outside the study area and receives pre-ART or ART care for the first time from a study clinic during the six month recruitment period
- Participants become eligible for study inclusion on the 4th day following a missed clinic appointment, provided the patient has not transferred care to another clinic prior to the 4th day, moved outside the study area or died. Participants who miss a study visit by >3 days but return to clinic before recruitment takes place are still eligible for study enrollment.
- Must currently reside on Mfangano, Remba or Ringiti Island.
- Must be conversant with one of the commonly spoken languages within the study area (i.e. DhoLuo, Swahili or English; prior experience indicates that this represents >99% of the adult population).
- Must be ≥18 years of age as of the date of study eligibility.

### Subject Exclusion Criteria

- Eligible participants who reside in the Mfangano East sub-location will be excluded from participation in this study. Many of these patients have already participated in the microclinic intervention as part of the Mfangano Island Healthy Network Impact Study.
- Participants planning on moving permanently out of the study area within the next six months will be excluded.
- Participants who, should they be randomized to the intervention arm, would be unwilling to participate in a microclinic will be excluded from study enrollment.

## Sampling

*Sample Size Calculation*

Sample size calculations were generated based on preliminary data from the Mfangano Island Healthy Network Impact Study (MIHNIS). The MIHNIS study was a quasi-experimental study with the intervention delivered to one community and neighboring communities acting as control groups. Additionally, the proposed clinic sites were visited in September 2014 to assess rates of missed clinic appointments to help ground sample size estimates in the realities of each individual clinic.

During the six months prior to delivery of the intervention in the MIHNIS study, 268 of 410 (65%) patients on ART at the Sena Health Center missed a clinic visit by >3 days. Of these, 238 (89%) joined the study. Among the control group in the MIHNIS study, 36 of 145 (25%) participants who missed a clinic visit by more than 3 days during the 6 months enrollment period had a 90-day clinic absence within the following 12 months. Among patients eligible for the intervention and who missed a clinic visit by >3 days during the enrollment period, 72 of 93 (77%) actually participated in the microclinic intervention. In the MIHNIS study participants in the intervention community had a more than 50% lower rate of 90-day disengagement than those in the control community, regardless of intervention uptake.

Thus, we assume an event rate of 0.25 in the control group and 0.125 in the intervention group. Setting alpha to 0.05 and beta to 0.2 and assuming an average of 2 participants per group with a coefficient of variation of 0.25, we will need 156 index participants per study arm. This sample size accounts for non-independence of outcomes introduced by the clustered nature of the intervention. Allowing for 10% participant attrition, we would need to sample 175 participants per study arm. The MIHNIS study ascertained outcomes for 98.6% of study participants, thus the allowance for 10% attrition in the proposed study is conservative.

The accessible population for this study includes all patients in HIV care and treatment, regardless of ART status, at the Sena (excluding patients residing in the East sub-location), Yokia, Ugina, Nyakweri, Wakula, Soklo, Remba and Ringiti Health Centers. Excluding patients residing in the Mfangano East sublocation from the total in Table 1, results in approximately 1500 current adult patients in these clinics. Extrapolating data from the MIHNIS study would suggest that 65% of these patients would become eligible for the Kanyakla Study during study enrollment. However, based on more recent observations at the included study clinics, we expect that only about half of the expected number of patients will become eligible. If we assume that 32% will become eligible that 75% of those who are elibigle will be willing to participate in the study, we will have an accessible population of 365 or approximately 180 per arm. Thus, because the accessible population is larger than the estimated sample size, we will extend our sample size to include up to 180 participants in each arm to allow for errors in these sample size calculations.

*Sampling Procedure*

Sampling will take place at included study clinics on a bi-weekly basis. Study staff will use information from the clinic daily activity log, master facility log and defaulter logs to identify all eligible patients who have missedclinic visits by >3 days. All eligible patients will be sampled for the study.

## Subject Recruitment and Enrollment (Figure 1)

Following sampling at the clinic, study staff will coordinate with clinic staff to obtain locator information and attempt to locate the potential participant in the community. Once identified, study staff will work with clinic staff to locate the patient to both encourage return to the clinic and invite them to join the study.

After explaining the study and answering all questions, eligible participants will be invited to enroll. Participants will be read the study consent form and will be asked to sign. If patient is illiterate, the participant will be asked to identify a witness who can co-sign the consent and help ensure that the participant fully understands all risks and benefits of the study.Following enrollment, participants will be randomized to either the intervention or control arm. Randomization will be conducted using sealed envelopes stratified by clinic site. Staff will open the next sequentially numbered envelope and will notify participants of their randomization allocation.

Participants randomized to intervention will be invited to form ‘microclinic’ groups. Microclinic formation involves recruitment of five to ten members of their social networks who they commonly rely upon for support (ie family members, friends, neighbors, co-workers, church members, etc). Study staff will assist in group recruitment and formation according to the preferences of the participant (i.e. participant will be asked whether they want to approach potential group members themselves or whether they want study staff to confidentially approach potential group members to invite them to participate). This process mirrors that used in our previous Mfangano Island Healthy Network Impact study (MIHNIS).

Participants randomized to control will be told that they are eligible to form microclinic groups following the conclusion of the study. They will be counseled on the importance of social support in their HIV care and will be clearly advised that assignment to the control group should not prevent them from discussing their HIV care with those close to them. As is true for all participants who are recruited for the study, they will be advised to return to the clinic. Beyond the counseling to return to clinical HIV care provided by study staff, standard of care for patients who have missed a clinic visit is to receive a follow-up visit from clinic staff to facilitate return to care. Study staff will collaborate with clinic staff to ensure that all study participants receive a visit from study staff and clinic staff to encourage return to care.

Orientation meetings will be conducted on a bi-monthly (every other month) basis with all newly formed microclinic groups. This meeting will include the following:

- The microclinic intervention will be explained to all prospective group members and a brief orientation to the curriculum will be provided.
- Study enrollment of social network members who were not originally enrolled through eligibility determination at the clinic. These ‘social network members’ will be consented for study participation (See Appendix I, Consent document for Microclinic Group Members), but will not be included in primary study analysis. Data from these participants will only be used for purposes of understanding the characteristics of those who were selected for microclinic participation and how their characteristics impact outcomes among index participants. For ‘social network’ participants, study participation will involve survey administration and data collection on participant HIV and clinic status in order to understand microclinic group composition. Study enrollment is voluntary and refusal will not prevent social network group members from participating in the microclinic group meetings. Aside from reasons for refusal, no data will be collected for social network participants refusing study enrollment.
- All group members will undergo individual confidential HIV testing (group members who are known to be HIV-infected will attend a counseling session but will not be tested).

[figure not shown]

**Figure 1.** Participant flow diagram

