## Procedures

### Study Design Overview

This is an individual randomized control trial evaluating the impact of the social network-based microclinic intervention on engagement and retention in HIV care over twelve months of follow up among individuals who have missed a clinic appointment by >3 days.

Study enrollment will occur over a six-month period. Upon meeting eligibility criteria, study staff will trace participants in the community to enroll them in the study. Eligibility will be determined using an Eligibility Determination Form, adapted from the FACES Loss to Follow-Up form (Appendix A). Study staff will counsel all eligible participants to return to clinic. After this counseling session, study staff will explain the purpose of the study and the nature of the intervention. After answering all participant questions, interested participants will be consented to participate (Section IX.c and Appendix H). Following study enrollment, participants will be randomized to intervention or control arm. Those randomized to intervention will be invited to recruit their social network members to form a microclinic. Study staff will provide confidential assistance to help discreetly identify and recruit family, friends, and neighbors to join the program based on previous protocols developed during the Mfangano Health Net Microclinic Pilot Program. Participants randomized to the control arm will be invited to form a microclinic group after the conclusion of the study.

Baseline measurements for index participants (i.e. participants who are eligible based on missed clinic visit) will be taken at study enrollment, with study staff administering a survey to collect data on baseline participant characteristics (Appendix C). Reasons for initial disengagement from care will also be recorded.

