### Intervention

Index participants who are randomized to the intervention arm will be invited to form a microclinic group. As described above, study staff will assist participants in microclinic group formation in a confidential manner. Though groups are formed from the social networks of index patients, group members will not be made aware of the specific process by which groups are formed or the identiy of the index patient or patients within any given group. This procedure protects against unintended breach of confidentiality and also allows groups to focus on the health of all members rather than specific index group members.

Following group recruitment, newly formed groups will attend an orientation meeting. This meeting will provide an overview of the microclinic intervention, as well as time for ‘social network’ participants to enroll in the study, complete baseline data collection and participate in baseline HIV voluntary counseling and testing (see enrollment procedures in Section VIII.d).

Following the orientation meeting, all microclinic groups will progress through a series of six microclinic sessions. (Appendix J) Sessions will take place every two weeks, will be led by trained community health workers and will take place at a time and location of the group’s choosing. Study staff will provide training for the community health worker facilitators and will supervise facilitation to ensure that the intervention is delivered as intended. Session topics for the seven sessions are as follows:

1. Overview of HIV biology and Scope of HIV on Lake Victoria
2. HIV medication overview – how medications work and why they are important
3. Antiretroviral therapy and herbal medicine
4. Destigmatization and group social support
5. Being an active patient
6. Confidentiality

[Group disclosure]

1. Post-group disclosure debriefing and the way forward

Following completion of the sixth group session, microclinic group members will be offered the opportunity to participate in Voluntary Counseling and Testing and group HIV status disclosure to other microclinic group members. Participation will be strictly voluntary and the sixth microclinic session will extensively cover the topic of group confidentiality and the importance of not pressuring or stigmatizing group members who do not want to participate in the process.

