Participant confidentiality is of paramount importance to the study investigators and staff and extreme caution will be taken to avoid any breaches of confidentiality. Study staff will be thoroughly trained in research practices and confidentiality, as well as proper handing of study documents. Data collected from participants will be de-identified at the time of data collection and will only be linked to identifying information through the unique study ID. As discussed above, identifying information and study datasheets will be kept in separate locked file cabinets located in a locked room dedicated only for research activities.

Participants will be advised that, by nature, group interventions such as the microclinic intervention have an inherant risk that confidentiality will be breached by a fellow group member. To minimize this risk, a substantial portion of the microclinic curriculum focuses on the importance of creating a safe space for all group members, emphasizing that all discussion that occurs within the setting of the group must not be shared with those outside the group.

- 1. **Study Discontinuation**

Inadaquate participant enrollment is the only reason why the study will be prematurely discontinued. Inadequate enrollment is defined as <50 participants enrolled in the study at the end of the 6 month enrollment period.

- 1. **Alternatives to Study Participation**

The alternative to study participation is not to participate. This will not in any way affect potential patients’ access to benefits from FACES or OHR services.

- 1. **Risks and Benefits of Study**

1. **Potential risks and discomforts**

The main risk of this study is breach of confidentiality or harm to reputation resulting from unintended HIV status disclosure.

1. **Steps being taken to minimize potential risks or discomforts**

Both study staff and microclinic group members will be trained on the importance of maintaining confidentiality. Additionally, all study documents will be de-identified at the time of data collection and stored separately from identifying information.

1. **Potential direct benefits to study subjects**

There is no direct benefit to study subjects. The intervention may provide benefit, but as there is currently equipoise regarding the efficacy of this intervention, this cannot be considered a benefit.

1. **Potential benefits to society**

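### The recruitment and orientation procedures do not assure the promise that group members will not learn who the index patient is

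*Protocol*

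**What the plan says.** **The assurance.** The Intervention section says that "group members will not be made aware of the specific process by which groups are formed or the identiy of the index patient", and gives the reason: "This procedure protects against unintended breach of confidentiality".

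**How groups are recruited.** Under Subject Recruitment and Enrollment, the "participant will be asked whether they want to approach potential group members themselves" or would rather have study staff make a confidential approach. Both routes are open, at the index patient's preference.

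**What happens at orientation.** The agenda in the same section includes "Study enrollment of social network members who were not originally enrolled through eligibility determination at the clinic". For index patients, consent comes first and the survey goes with it: "Baseline measurements for index participants (i.e. participants who are eligible based on missed clinic visit) will be taken at study enrollment" (Study Design Overview). That section also says that all prospective social network participants are to be invited to enrol when the group enrols. Two provisions soften the contrast:

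- "Study enrollment is voluntary and refusal will not prevent social network group members from participating in the microclinic group meetings".
- Every member has an individual, confidential testing step, and "group members who are known to be HIV-infected will attend a counseling session but will not be tested".

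**The risk.** Ethical Considerations states: "The main risk of this study is breach of confidentiality or harm to reputation resulting from unintended HIV status disclosure". The listed steps to reduce it are training of staff and group members in confidentiality, and de-identified, separately stored documents.

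**The concern.** An index patient is, by eligibility, someone in HIV care who missed a clinic appointment by more than 3 days. Learning who the index patient is could therefore reveal both HIV infection and a lapse in care. The protocol treats that identity as something to protect, and presents the non-disclosure procedure as the protection.

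Two features of the plan work against it. A member invited in person knows who did the inviting. At orientation, index patients follow a shorter path than everyone else in a small group of people who mostly know one another. The second feature also arises when staff recruit confidentially, which is the route meant to shield the patient.

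What is at stake is participant safety. Orientation comes before all the sessions, and voluntary group disclosure is offered only after the sixth, so any inference made at orientation comes before patients have decided whether to disclose.

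**Working it through.** No formula or reported figure is involved. The check sets the sections side by side.

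**Step 1. Is the assurance qualified?** No. The Intervention section covers both the formation process and the identity of the index patient. It does not separate groups recruited by staff from groups recruited by the patient.

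**Step 2. Does personal recruitment conflict with it?** In part. Someone approached personally by the index patient knows whose invitation it was, and so knows something about how the group was formed. The group member survey allows for this, listing recruitment by a friend as a coded reason for joining. Knowing the inviter is still not the same as knowing that the inviter is HIV-infected or missed a visit.

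**Step 3. Who goes through what at orientation?**

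| Step | Index patient | Network member who enrols | Network member who refuses |
| --- | --- | --- | --- |
| Invited to consent at orientation | No, done earlier | Yes | Yes |
| Baseline survey by study staff at orientation | No, done earlier | Yes | No |
| Private HIV testing or counselling session | Yes | Yes | Yes |

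Non-enrolment does not single out index patients, because refusers are also not enrolled. Being left out of the invitation does: every network member is to be asked, and index patients have already been asked. The testing step is level, since known HIV-infected members attend a counselling session in place of the test.

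**Step 4. How visible is the difference?** The Informed Consent Process text requires consent to be taken individually in a private location. That protects the content of the conversation. The protocol does not say whether other members can see who is called. Visibility is therefore plausible but not documented.

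**Step 5. How small is the group?** The Abstract gives 5 to 10 individuals and the Sampling section assumes an average of 2 index participants per group. If the 5 to 10 includes the index participants, 5 − 2 = 3 to 10 − 2 = 8 members are invited to enrol and about 2 are not. This describes the contrast; it is not a probability of identification.

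**Step 6. How early is it?** Sessions are fortnightly and disclosure is offered after the sixth. If the first session falls two weeks after orientation, the gap is at least 6 × 2 = 12 weeks. If it follows orientation at once, the gap is at least 5 × 2 = 10 weeks.

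**Step 7. Do the listed mitigations cover this?** Training and de-identified records address what people say and what documents show. Neither addresses identification through the procedure itself.

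**The case against.** The case against acting is a serious one.

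- The assurance can be read as a limit on what staff reveal, not as a guarantee that nobody can guess.
- Self-recruitment is the patient's own choice, with confidential staff recruitment as the alternative.
- Groups are mixed by HIV status by design (Introduction/Background, Study Design Overview) and may hold several index patients.
- The Community Mobilization section describes a public programme-expansion message intended to shield groups from stigma over how they were formed.
- Consent is private, and every member attends a private testing or counselling session.
- Subject Confidentiality says participants will be advised that group interventions carry an inherent risk of breach by a fellow member.
- Room logistics often belong in an operations manual, and the consent forms (Appendices H and I) are not in the text reviewed, so a warning in them cannot be excluded.

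All of this stands as a limit on the conclusion. It rules out two stronger readings that a reader might draw. One is that index patients are the only members not enrolled at orientation; the refusal provision contradicts it. The other is that the protection fails; the documents show a weakness, not a certain disclosure.

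The objection does not remove the mismatch. The assurance is written without the limit that the objection reads into it. The advice about breach concerns what fellow members may pass on, not what the study's own procedure may show. The recruitment section mentions no explanation to index patients of what a personal approach reveals before they choose.

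**Conclusion.** The point holds as a low-cost improvement in participant safety. The procedures for recruitment and orientation do not assure the unqualified statement in the Intervention section, and the harm concerned is the one the protocol names as its main risk. Index status is not certain to be revealed.

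The documents support no count of identified patients. A reader might apply the pilot's disclosure rate of over 84% and conclude that up to 0.16 × 175 = 28 intervention index patients who would not choose to disclose could be exposed. That figure does not hold up:

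- The 84% is a share of all pilot participants, in groups totalling nearly 550 community members, and not of index patients.
- It assumes that every index patient joins a group. With the earlier study's uptake of 72 of 93 (77%), about 0.77 × 175 = 135 would join, and the same borrowed rate gives 0.16 × 135 = about 22.
- Both figures assume that every non-discloser is identified. The share of patients who recruit personally and the chance that members draw the inference are unknown.

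The conclusion rests on one assumption about practice: that, in a small group, members may notice who is and is not invited to consent and be surveyed. Sample size, power and analysis are unaffected.

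**What to change.** 1. **Orientation (Subject Recruitment and Enrollment; Intervention).** Send every attendee, index patients included, through the same private stations. Index patients can use the consent and survey slot for something else, such as a locator update. This extends the levelling already used for HIV testing.
2. **Recruitment choice (Subject Recruitment and Enrollment).** Before the index patient chooses how members are approached, tell them that a personal approach shows them to be the person whose network formed the group.
3. **Assurance (Intervention).** Limit the statement to what study staff disclose about group formation and index identity.

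The cost is procedure and script wording, plus a few extra minutes of existing staff and index-patient time at orientation. No new data, staff or participants are needed.
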